## Abstract

**Background:**

It is expected that in 2020 more than 17,000 cases of colorectal cancer will be diagnosed in The Netherlands. To date, patients are included in a surgeon-led follow-up programme whose main focus is recurrence detection. However, patients often experience multiple physical and psychosocial problems. Currently, these problems are not always encountered. More care by a generalist is suggested as a solution. Furthermore, patients prefer to undergo rehabilitation in their own environment and to be more involved in their own health care. eHealth applications might enhance this. Oncokompas^2.0^ is an online self-management application which facilitates access to supportive care. This study aims to evaluate primary care follow-up and aftercare in comparison with secondary care follow-up and aftercare for patients with colon cancer. Second, the added value of Oncokompas^2.0^ to care will be assessed.

**Methods/Design:**

This is a multi-centre 2 × 2 factorial randomised controlled trial with a calculated sample size of 300 patients. Patients with stage I, II, or III colon carcinoma are eligible. Patients will be randomly assigned in four groups: (1) usual follow-up visits and aftercare provided in secondary care, (2) usual follow-up visits and aftercare provided in secondary care with additional use of Oncokompas^2.0^, (3) follow-up and aftercare in primary care, and (4) follow-up and aftercare in primary care with additional use of Oncokompas^2.0^. The primary outcome is quality of life. Secondary outcomes include physical outcomes, psychosocial outcomes, number of investigations, referrals and related communication between secondary and primary care, (time of) recurrence detection and protocol adherence, attention to preventive care, self-management of patients, patient satisfaction, and preference of care at the end of the trial. Data collection will be done by questionnaires and extractions from electronic medical records.

**Discussion:**

The results of this study will provide evidence, which has been scarce to date, on prominent general practitioner involvement in care for colon cancer patients after initial treatment. Also, it evaluates the efficacy of an eHealth application to enhance patient empowerment.

**Dutch trial register:**

NTR4860 (registered on 2 October 2014)

## Background

It is expected that in 2020 more than 17,000 cases of colorectal cancer will be diagnosed in The Netherlands [1, 2]. Currently, in The Netherlands after initial treatment, patients are typically included in a surgeon-led programme whose main focus is detection of recurrence and metachronous tumours; in general, this is called follow-up. There is evidence that intensive follow-up programmes improve (overall) survival of patients with colorectal cancer [3, 4]. The Dutch guideline includes periodic visits combined with a carcinoembryonic antigen (CEA) blood test, imaging of the liver, and colonoscopy during the first five years after curative treatment [2]. Given that this follow-up programme is convenient to carry out, it is only a small step to hand over management of follow-up to general practitioners (GPs), especially since most patients have chronic co-morbid conditions and are familiar with their GP. Furthermore, primary health-care use is increased the first five years after colorectal cancer diagnosis [5].

Patients with cancer often experience multiple physical, functional, and psychosocial problems during and after the initial treatment phase [6]. These symptoms can cause considerable distress. Care with the purpose of alleviating these symptoms is called aftercare or supportive care [3]. Goals of aftercare are improvement of physical condition, finding emotional and social balance, coping with disabilities, and restoring autonomy by increasing self-efficacy and regaining confidence [7]. Currently, follow-up visits in secondary care do not always address these aspects, and studies suggest that only a small number of distressed patients are identified and supported [8–10]. Recently, our research group conducted a large cross-sectional survey in The Netherlands among patients, surgeons, and GPs in which current surgeon-led aftercare and possible future GP-led aftercare were evaluated. Only half of the patients were satisfied with the identification and treatment of psychosocial problems. Moreover, three out of four surgeons stated that, owing to their lack of time and experience, psychosocial problems in particular possibly received not enough attention [11]. Both the Dutch Health Council and the Dutch Cancer Foundation suggested more care by a generalist as a solution to these problems [3, 12].

The number of cancer patients with co-morbidity is expected to increase as a result of aging of the general population [12, 13]. Besides giving attention to pre-existent co-morbidity, health-care professionals should be aware of newly developed co-morbidity after cancer treatment. Therefore, preventive care is important for all survivors of colorectal cancer. Moreover, disease-free survival of patients with colorectal cancer is increased in those with higher levels of physical activity. Nevertheless, colorectal cancer survivors have the highest percentage of sedentary lifestyles among survivors of malignancies, and studies suggest that professionals miss opportunities to counsel cancer survivors—in particular, colorectal cancer survivors—about healthy behaviours [14].

The guidelines of the Dutch National Gastrointestinal Cancer group do not offer clear recommendations about which health-care professional should coordinate care after initial treatment [2]. The Dutch Cancer Society’s Signalling Committee on Cancer emphasizes the importance of primary care in cancer management [12]. GPs with their generalist and broad view, accessibility, continuity of care, experience with chronic disease management, and wide network of health-care providers might therefore be the most appropriate health-care professional to provide aftercare [15]. Few studies report on primary versus secondary care follow-up of breast and colonic cancer [16–18]. These studies show no significant difference for quality of life, recurrence rate, and anxiety. However, GP-led cancer follow-up was more cost-effective than hospital follow-up and this was due mainly to a difference in organisational and physician costs.

Furthermore, it would be preferable for as much of the rehabilitation as possible to be conducted in the patients’ own environment. Besides an expanded role for GPs, a more central role of the patient in management of his or her own health is emphasized by the Chronic Care Model [19]. Self-management or patient empowerment is defined as the individual’s ability to manage symptoms, treatment, physical and psychosocial consequences, and lifestyle changes inherent to living with a chronic condition [20]. Evidence shows that web-based interventions for patient empowerment can improve care for patients with cancer [21, 22]. The aim of eHealth applications targeting patient empowerment is to enable patients with cancer to positively influence their treatment and rehabilitation, in keeping with the professional execution of aftercare, by providing them with timely insight into, for instance, their individual state of health and their treatment stage or needs, and by offering personal lifestyle coaching based on their actual quality of life. An important example of these eHealth applications is Oncokompas^2.0^. In Oncokompas^2.0^, cancer survivors can monitor their quality of life by means of participant-reported outcomes (PROs) (“Measure”) and this is followed by automatically generated tailored feedback (“Learn”) and personalised advice on supportive care services (“Act”) [10, 23]. It is based on the Dutch guideline Cancer rehabilitation and Screening for the need of psychosocial care [7, 24]. The above-mentioned developments are subjects of the I CARE study because, to date, robust research on a more prominent role for primary care and the use of eHealth applications in the follow-up and aftercare for colon cancer patients after initial treatment is missing and possible benefits in terms of patients’ satisfaction and quality of life should be further assessed.

Therefore, the aims of this study are to determine the efficacy of GP-led follow-up and aftercare compared with secondary care-led follow-up and aftercare among patients with colon cancer and to determine the added value of the eHealth self-management application Oncokompas^2.0^. We hypothesize that GP involvement improves aftercare and preventive care, resulting in improved quality of life and patients’ satisfaction. Furthermore, we hypothesize that a GP-led recurrence detection programme (follow-up) for patients after curative treatment of colon cancer leads to at least equal detection of recurrences and subsequently an equal number of curative recurrence resections. Finally, we hypothesize that usage of Oncokompas^2.0^ facilitates patients’ self-management and personalised access to supportive care in cancer.

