### Outline of the study and data collection procedures

Approximately 3–4 weeks postoperatively, patients will be seen at the surgical outpatient clinic. At this visit, a clinical examination will be performed, and information about the histology and results of the surgery will be shared with each patient. Patients not receiving adjuvant chemotherapy and eligible for study inclusion will be asked for their informed consent. Also, patients who need adjuvant chemotherapy and are eligible for study inclusion will be asked for their informed consent. However, before final inclusion in the study, the patients will be referred to the oncologist for chemotherapeutic treatment. After completion of adjuvant chemotherapy, these patients will be included definitively.

After a patient has given informed consent, the GP is contacted if he or she wants to participate in the study. If the GP participates, the patient is finally randomised.

If a patient declines randomisation (or the GP of the patient declines randomisation), the patient is asked to participate in a patients’ preference group and will receive surgeon-led follow-up and aftercare. Patients allocated to GP-led follow-up may be referred back to the hospital at any time during the study. Similarly, patients in the surgeon-led groups are free to consult their GP any time during the study. Subjects can leave the study at any time for any reason without any consequence.

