### Analysis

#### Sample size

The sample size calculation is based on the primary endpoint: quality of life. In accordance with previous studies, we consider an effect of 10 units of improvement of the EORTC QLQ C30 to be clinically relevant [34]. To detect an intervention effect of 10 units of change (standard deviation of 20) in quality of life, we will need 64 participants in each group (alpha of 0.05 and power of 80 %). As we expect some drop-out, we aim for 75 patients in each group. The total sample size is therefore 300 patients. Given the sample size calculation and the factorial design of the study, the assumptions are made that the effects of the two interventions are independent and that there are no important interactions (synergy).

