#### Analysis of main study parameters

All analysis will be performed according to the intention-to-treat principle. Crude data are presented with statistical comparison made between randomisation groups on the basis of chi-squared tests for binary or categorical data, the *t* test or analysis of variance as appropriate for comparing group means, and the Kruskal-Wallis test for comparing medians. For continuous normally distributed data, the analysis-of-variance test will be used. The primary analysis will be the comparison between factors, and the comparison between study arms will be part of a secondary, exploratory analysis. For these purposes, univariate and multiple linear or logistic regression analyses will be performed. Quality of life will be assessed through multi-level modelling. A two-sided *P* value of less than 0.05 will be considered statistically significant. Nevertheless, in all appropriate cases, 95 % confidence intervals will be given. Changes in health status and valuation over time will be measured by using the questionnaires mentioned above. Next to validated questionnaires and prospective monitoring of the trial endpoints, extractions from the GPs’ EMR and patients’ hospital records will be used to complete the data.

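### The hypothesis of at least equal recurrence detection has no matching criterion: the only stated rule is a two-sided difference test at P<0.05 with no margin

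*Protocol article*

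**What the plan says.** The last paragraph of the Background sets out hypotheses of different kinds. For quality of life the claim is superiority: "GP involvement improves aftercare and preventive care, resulting in improved quality of life and patients’ satisfaction". For recurrence it is that a GP-led programme "leads to at least equal detection of recurrences and subsequently an equal number of curative recurrence resections".

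The section Analysis of main study parameters gives one criterion for all comparisons: "A two-sided *P* value of less than 0.05 will be considered statistically significant". The methods it lists are tests of difference (chi-squared, *t* test, analysis of variance, Kruskal-Wallis) and regression models. It adds "Nevertheless, in all appropriate cases, 95 % confidence intervals will be given", makes the comparison between factors primary, and says "All analysis will be performed according to the intention-to-treat principle".

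The section Sample size derives 64 patients per group from a quality-of-life difference of 10 units with a standard deviation of 20, raised to 75 per group for drop-out. It contains no calculation for recurrence or resection. The Abstract lists recurrence detection, including its timing, as a secondary outcome. Under Quality control, the DSMB assesses every recurrence for diagnostic delay caused by the protocol.

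**The concern.** At-least-equal detection needs a limit on how much worse GP-led follow-up may be. An equal number of resections needs limits on both sides. A difference test at P<0.05 has neither. It can show that the arms differ, but it cannot show that they are alike. The only result of this rule that could appear to confirm the hypothesis is a non-significant one, and in a trial sized for another endpoint that result is likely even when detection is materially worse.

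The outcome is secondary, but it carries weight. The Background cites evidence that intensive follow-up improves survival, and the Discussion says the trial assesses safety over five years. An unsupported statement that detection is equal could influence a decision to move follow-up to GPs.

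**Working it through.** **1. The plan's own figure.** Inputs from Sample size: difference 10, SD 20, two-sided alpha 0.05, power 80 %.

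n per group = 2 × [20 × (1.96 + 0.842) / 10]² = 62.8, so 63 by the normal approximation. The two-sample *t* test gives 63.8, so 64. The stated 64 is reproduced, and it concerns quality of life only.

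**2. Numbers available for the recurrence comparison.** Four groups of 75 compared at factor level give 150 GP-led v 150 surgeon-led. If the quality-of-life drop-out allowance also applied here, it would be 2 × 64 = 128 per level. That is pessimistic, because GP and hospital records will be used to complete the data.

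**3. Precision.** The document gives no recurrence rate, so 10 to 25 % detected over follow-up is an assumption. With equal true rates p,

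half-width = 1.96 × √[2p(1−p)/n].

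For p = 0.15, n = 150: 1.96 × √(0.255/150) = 0.081, or 8.1 points.

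**4. Chance of P≥0.05 when GP-led detection is truly 5 points lower.** The 5 points are also illustrative. With p₁ surgeon-led, p₂ = p₁ − 0.05 and p̄ their mean:

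- SE₀ = √[2p̄(1−p̄)/n]
- SE₁ = √[(p₁(1−p₁) + p₂(1−p₂))/n]
- power = Φ[(0.05 − 1.96·SE₀)/SE₁]

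For 15 % v 10 %, n = 150: SE₀ = 0.03819, SE₁ = 0.03808, and (0.05 − 0.07485)/0.03808 = −0.653. Power is about 26 %, so P≥0.05 occurs about 74 % of the time.

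| Assumed surgeon-led detection | Half-width, 150 v 150 (points) | P≥0.05 if GP-led is 5 points lower | Half-width, 128 v 128 (points) | P≥0.05 if GP-led is 5 points lower |
|---|---|---|---|---|
| 10 % | 6.8 | 62 % | 7.4 | 67 % |
| 15 % | 8.1 | 74 % | 8.7 | 77 % |
| 20 % | 9.1 | 79 % | 9.8 | 82 % |
| 25 % | 9.8 | 82 % | 10.6 | 84 % |

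If true recurrence is the same in both arms, a 5-point loss is half of all recurrences at the 10 % rate and a fifth at the 25 % rate.

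**5. Curative resections.** If 5 % had one (an assumption), 0.05 × 150 = 7.5 would be expected per factor level. The half-width is 1.96 × √(0.095/150) = 4.9 points, about the size of the rate itself. A true halving would give P≥0.05 about 79 % of the time. With so few events the normal approximation is rough.

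**6. What a margin would ask for.** Non-inferiority n per level = 2p(1−p)(1.96 + 0.842)²/m², for equal true rates, one-sided 0.025 and 80 % power; the margins m are illustrative.

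| Assumed rate | n per level, 10-point margin | Power with 150 | n per level, 5-point margin | Power with 150 |
|---|---|---|---|---|
| 10 % | 142 | 82 % | 566 | 30 % |
| 15 % | 201 | 68 % | 801 | 23 % |
| 20 % | 252 | 58 % | 1005 | 19 % |
| 25 % | 295 | 52 % | 1178 | 17 % |

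The one combination with adequate power, a 10-point margin at a 10 % rate, is not useful: 10 − 10 = 0, so the margin would tolerate the loss of all detection.

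**The case against.** **The consequence is inferred.** A reader might infer that the trial will report a non-significant result as equality. The article does not say so. It promises 95 % confidence intervals straight after the P-value rule, and an interval would show how large a loss remained possible. That stands: the most one can say is that a non-significant result could be read that way. The intervals still have no bound to be compared with, so they do not define at least equal.

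**A margin may be elsewhere.** Sizing a trial on its primary endpoint is normal, and a journal article commonly leaves a secondary outcome's margin to the full protocol or analysis plan. The absence of a margin would be no finding by itself. What remains is that the article states both a hypothesis and a blanket rule, and the rule cannot confirm the hypothesis.

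**Patient safety is monitored.** The DSMB meets every 45 patients or every 6 months and assesses all recurrences for delay. This protects participants during the trial. It is case review, though, not a test of the between-arm hypothesis.

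**Intention-to-treat.** Because "Patients allocated to GP-led follow-up may be referred back to the hospital at any time during the study", a reader might infer that intention-to-treat pulls the arms together, and that a set restricted to patients who stayed in allocated care is needed. The document does not support that. Under Intervention 1, the instructions to GPs for suspected recurrence consist mainly of prompt re-referral, so return to hospital is part of the GP-led pathway. Such a set could remove, from one arm only, the very patients whose recurrence was suspected.

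**The proportion is not the whole endpoint.** The Abstract includes the time of detection, and the DSMB looks for delay. A delay could leave the five-year proportion almost unchanged, so the figures above describe only part of the question.

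**Conclusion.** The concern holds as a mismatch between a stated hypothesis and the stated rule. With 150 v 150 and assumed detection of 10 to 25 %, the interval extends about 6.8 to 9.8 points either side of the difference, and a true 5-point loss is non-significant about 62 to 82 % of the time. P≥0.05 would therefore not support at least equal detection, and with few expected events it would say even less about an equal number of resections. The recurrence rate, resection rate, size of loss and margins are all assumptions; the direction of the conclusion does not change across the ranges shown.

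A reader might take this as a flaw in the trial's main question. It is not. The outcome is secondary, and the quality-of-life sample size reproduces. The point should be settled before the recurrence results are analysed, but it is not a must-fix for the primary question.

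**What to change.** Reword the hypothesis as estimation: the GP-minus-surgeon difference in recurrence detection, including time to detection, and in curative resections, each at factor level with a 95 % confidence interval. State that P≥0.05 will not be reported as equal or at least equal, and give the interval width expected with 150 per level.

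If the claim of at least equal detection is kept, prespecify and justify a margin and judge the claim by the confidence bound, acknowledging that 300 patients give limited power for most margins considered above.

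Keep intention-to-treat, and do not make the conclusion depend on a set limited to patients who stayed in allocated care.

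The estimation option changes wording only, with no added patients or data. Its price is a weaker safety claim: the trial would report how large a loss of detection it can rule out, not that there is none.

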## Methods/Design

This is a multi-centre 2 × 2 factorial randomised controlled trial. Two randomisation procedures (at the same moment) will be undertaken: one to create two groups for surgeon-led—usual care (i.e., control group)—versus GP-led follow-up and aftercare and a second randomisation for allocation of the eHealth application Oncokompas^2.0^. This factorial design results in four groups on a 1:1:1:1 ratio (Fig. 1):Usual follow-up visits and aftercare provided in secondary care (surgeon-led);Usual follow-up visits and aftercare provided in secondary care (surgeon-led) with additional use of the eHealth application Oncokompas^2.0^;Follow-up and aftercare in primary care (GP-led);Follow-up and aftercare in primary care (GP-led) with additional use of the eHealth application Oncokompas^2.0^.

**Fig. 1 Fig1:**
[figure not shown]
Study flow chart. *GP* General practitioner

Randomisation will be performed centrally at the Academic Medical Centre in Amsterdam by using block randomisation to balance patient characteristics within each group on the basis of two variables: age and tumour stage. If a second patient of an already-participating GP is included, this patient (and all subsequent patients) will be allocated to the same follow-up/aftercare arm (i.e., primary or secondary care). The chance that two patients of the same GP will be diagnosed with colon cancer in the study period, will be eligible for inclusion in the study, and give informed consent is small. Nevertheless, we avoid having two patients of the same GP receive different care (primary care-led versus secondary care-led follow-up) as this will result in contamination. Owing to the nature of the intervention, it is not possible to conceal the allocation group from either participants or clinicians. However, the primary researchers are not involved in subsequent follow-up/aftercare appointments in any way. Recruited patients will not be informed about other patients recruited in the same trial. Similarly, no information regarding trial progress will be revealed to the participating GPs or surgeons.

The study will be conducted in eight hospitals. The number of segmental colonic resections for cancer in the participating centres ranges between 60 and 160 patients per centre annually.

If a patient (or GP) declines randomisation, the patient is asked to participate in a patients’ preference group (Fig. 1). In this arm, baseline data similar to those of the randomised study arms are gathered, but the allocation is based on the patients’ treating surgeon and patient preference.

